#### Data collection

In Phase III, we will assess acceptability (using the toolkit) and feasibility (implementing the toolkit in practice) and identify outcomes with children and families.

Participating families will be invited to discuss their particular challenges with NIV and their desired outcomes from an intervention with the clinical nurse specialist during their routine clinical appointments or over the phone. The researcher will liaise with the clinical nurse specialist prior to the consultation as to whether they want to introduce the toolkit at the beginning or end of the consultation; the timing of the introduction will not have an impact on the study outcome.

In face-to-face/virtual appointments, the clinical nurse specialist will show and describe the contents of the toolkit and invite families to discuss each intervention using a ‘Think Aloud’^30^ approach and describe their thoughts and feelings of their own situation. Families will be asked to choose the intervention they want to test and identify which outcome they hope the intervention will impact, for example, school attendance, reduction in night-time waking, etc. They will be asked to test the intervention for 2 weeks. The researcher will observe and document the chosen intervention, outcome and decision-making in field notes.

It is likely that clinical appointments with families who have lower levels of adherence will be more likely to result in a recommended clinical change (eg, new interface, changed pressure settings, introduction of a new comfort measure, etc) compared with families who do not report any issues and use NIV consistently. Families who have a recommended clinical change will be asked to start testing the intervention 2 weeks after the introduced change; families with no clinical changes will be asked to start immediately.

After the initial consultation, the researcher will collect baseline data related to the intervention and outcome from families.

Once home, during the 2-week test period, parents and children will be asked to record their experience of using the intervention, including the duration and any challenges they faced. They will be asked to wear an Actiwatch or equivalent device overnight during the 2-week trial period (children only) and keep an Actigraphy diary (older children/parent) to record data about sleep patterns and routines (eg, time child went to bed).

After 2 weeks, the researcher will visit the family at their home and ask the parents and, where possible and appropriate, the child to participate in a short semi-structured reflective interview (a debrief) about whether they used their chosen intervention as anticipated (fidelity to the intervention), any particular challenges, whether it was acceptable in practice, how feasible it was to use and perceptions of the outcome measurement. Children will be offered a range of creative methods to describe their experiences, such as Talking Mats^31^ or Draw and Write. Parents and, where possible, children will be asked to complete a postintervention questionnaire on the outcome and intervention. The researcher will collect all equipment and download the ventilator data onto an encrypted USB drive. Actiwatch data in conjunction with the ventilator data will enable us to identify whether the child: (1) used their NIV during the 2-week period and (2) if they used their NIV when asleep. This will mitigate potential response bias, for example, if parents report that the intervention resulted in complete adherence and the ventilator data show that the ventilator was not used in the study period. These data will also be collected to assess whether the intervention has caused a decrease in adherence.

If families are unable to find a time when a researcher can visit their home within the 2–4 weeks period, the researcher will offer the family a phone call or virtual meeting to complete data collection activities and make arrangements for the download of ventilator data and the return of study equipment (Actiwatch and iPad).

All discussions and interviews will be audio-recorded with families’ permission and transcribed verbatim for subsequent analysis. Demographic data and clinical information will be extracted from medical records for both analysis and reporting purposes.

### Data analysis

#### Qualitative analysis

Qualitative analysis in Phase III will follow the Framework Analysis steps outlined in Phases I and II. The Phase III framework will seek to identify participants’ (positive and negative) experiences of using the intervention during the 2-week period, how the parent and child engaged with it, what (if any) impact it had on their child’s NIV use and the wider family household and if the intervention should be changed in any way. Parent entries in their diaries will be used to inform both the postintervention debrief as well as analysed in their own right and included in the Phase III frameworks.

#### Quantitative analysis

We will compare usage data (number of hours used per night and number of nights used) during the 2-week trial period and usage data from the 4 weeks prior to the most recent ventilator download (usually in the NIV clinic or at the most recent sleep study). Questionnaire data will be analysed using descriptive statistics and recruitment rates, retention and fidelity to the intervention will also be analysed descriptively.

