#### Recruitment

The sampling strategy for Phase III will be the same as Phases I and II but will additionally include the choice of intervention (ie, we will increase our invitation rates if participants choose the same interventions as previous participants).

All eligible families will be introduced to the study by a NIV staff member at the study site. Families will be approached to participate when they come for their NIV outpatient appointment/NIV sleep study (in person or digital appointment) or another GOSH appointment. When these options are not available, a letter will be sent with information sheets and consent forms, followed by a phone call by a study site member of staff to check that the information has been received and to ask if the family have any questions.

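### The usage comparator is tied to the last ventilator download, not to the start of the 2-week test, so for some families with no clinical change it may end well before the test

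*Protocol article*

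**What the plan says.** All references are to the protocol article.

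- **Quantitative analysis (Data analysis).** The test side of the comparison is fixed: "We will compare usage data (number of hours used per night and number of nights used) during the 2-week trial period". The other side is "usage data from the 4 weeks prior to the most recent ventilator download", and a parenthesis explains that this download is usually made in the NIV clinic or at the latest sleep study.
- **Data collection (Phase III), consultation.** Families discuss their difficulties and hoped-for outcomes "with the clinical nurse specialist during their routine clinical appointments or over the phone".
- **Data collection (Phase III), start of test.** After that consultation, "families with no clinical changes will be asked to start immediately". The baseline step described is information on the intervention and outcome, obtained from the family. A ventilator download is not mentioned there.
- **Data collection (Phase III), end of test.** At the home visit, "The researcher will collect all equipment and download the ventilator data onto an encrypted USB drive". The section gives the ventilator and Actiwatch data three uses: to show whether NIV was used in the 2 weeks, to show whether it was used during sleep, and to assess whether the intervention reduced adherence.

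No section sets a maximum age for the download that defines the comparator.

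**The concern.** A before-after comparison within a child is easiest to read when the two periods adjoin. Here the comparator hangs on a past clinical event. For a no-change family whose download is made at the consultation itself, the 4 weeks run up to the start of the test. For a no-change family consulted by phone, they may end at whatever earlier date the last download was made.

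Two things are at stake. Ordinary drift in use, illness or the school calendar could be mixed with any change during the test, and the question of whether the intervention lowered adherence depends on this comparison. Also, the recency of the comparator would depend on how the family was seen, so children would not be measured alike. With 10–12 dyads, a few old comparators could alter the descriptive picture.

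The point is framed for families with no clinical change. For the others, the change itself and a 2-week wait also fall between comparator and test, which is a separate matter.

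**Working it through.** The plan gives no figure for the lag, so there is none to reproduce. The check is a timeline.

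**Inputs**
- Comparator length: 4 weeks = 28 nights (Quantitative analysis).
- Test length: 2 weeks = 14 nights (Quantitative analysis).
- Start of test for no-change families: immediately after the consultation (Data collection).
- Time on NIV at recruitment: more than 3 months, taken as about 91 days at the lower end (Phase III Inclusion criteria).
- L, the days from the last download to the start of the test: not in the document. The values below are assumptions for illustration.

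**Position of the windows.** Let day 0 be the start of the test.
- The comparator runs from day −(L + 28) to day −L, with midpoint −(L + 14).
- The test runs from day 0 to day 14, with midpoint 7.
- Gap between midpoints = 7 + (L + 14) = L + 21 days.

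| L (assumed, days) | Comparator window | Midpoint gap (days) |
|---|---|---|
| 0 | −28 to 0 | 21 |
| 30 | −58 to −30 | 51 |
| 90 | −118 to −90 | 111 |
| 180 | −208 to −180 | 201 |
| 365 | −393 to −365 | 386 |

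**Short history on NIV.** A child about 91 days on NIV when the test starts has 91 − L days of NIV before the last download. A full comparator needs 91 − L ≥ 28, so L ≤ 63. With a longer lag the window is incomplete and falls in the child's first weeks of use.

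**Effect of anchoring to the test.** Ending the comparator at the start of the test sets L = 0. Every no-change family then has a midpoint gap of 21 days, whether seen in clinic or by phone.

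**Device memory needed.** If the download is made as the test ends: 28 + 14 = 42 nights. If it is made 2 weeks later, at week 4: 42 + 14 = 56 nights. The article also provides for families who cannot be visited within that period, so more could be needed.

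**The case against.** The case for leaving the rule alone has real parts.

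- **Purpose.** Phase III tests feasibility and acceptability, and Study outcomes leaves efficacy to a later pilot. No hypothesis test on usage is described. Two of the three uses of the ventilator data need no comparator, and the diaries and debrief can bring out other influences on use. This stands, and it limits the weight of the point.
- **Detail left to a fuller document.** An allowable lag is often set in the full protocol or SAP, and its absence alone would be no finding. But the article does more than omit a limit: it states an anchor, and following that anchor can give a non-adjacent comparator.
- **Trade-offs of the remedy.** Device memory is not described. The remedy gives no-change families their own definition plus a fallback, within a very small sample. Some of the 28 nights may also fall after the family was first approached about the study, when use might already have shifted. These are costs, but they do not make an older window the better default.

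A reader might also infer more than the article supports:

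- *That families seen by phone have no download at entry.* The article does not say so. It describes none at that point, and its wording on where downloads usually occur leaves room for others.
- *That families invited by letter have old comparators.* "When these options are not available, a letter will be sent with information sheets and consent forms" describes how they are invited. They may still be consulted in clinic with a download that day.
- *That this is the study's only comparator.* It is the only before-after comparison of device usage. Baseline data on the chosen outcome and a post-intervention questionnaire are also collected.

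**Conclusion.** The point holds as a weakness in how the comparator is anchored. As written, the rule allows a usage comparator that does not adjoin the test for no-change families consulted by phone. The planned end-of-test download may be able to supply one that does.

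Severity is minor to moderate. The comparison is descriptive, covers 10–12 dyads and is secondary to feasibility and acceptability, but it is meant to inform whether the intervention lowered adherence.

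The size is not known. It would be tempting to say that the comparator may be unlimited in age, or 3–6 months old. The first only means that no limit is stated, since routine follow-up may bound the lag in practice. The second needs a review interval that the article does not give. Nor does the article say how many dyads would be consulted by phone. The conclusion rests on one inference: that at least some phone consultations take place without a fresh download.

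**What to change.** In Quantitative analysis, for families with no clinical change, define the comparator as the 28 nights ending the night before the test starts, read from the ventilator download already planned at the end of the test. Where the device does not hold those nights, keep the current rule as fallback. For each child, report which definition was used and the days between the end of the comparator window and the start of the test.

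This also removes a small ambiguity. Once the test is over, the latest download is literally the end-of-test one, and the 4 weeks before it would include test nights. The parenthesis shows that this is not meant, but a definition tied to the start of the test leaves no doubt.

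The cost is a sentence or two in the analysis section, with no added visit or equipment. The downside is reliance on device memory, an assumption to be confirmed for the ventilators in use (at least 42 nights, more if the download is delayed), and a fallback definition for some children.

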### Feasibility and acceptability testing of the intervention toolkit

#### Inclusion criteria

Children aged 0–18 years who have a diagnosis of SDB, have been prescribed NIV for >3 months prior to recruitment and are under the care of the study site NIV team will be eligible to participate. Children will be ineligible to participate if they are medically dependent on NIV, receive NIV for palliation, have used NIV for <3 months or are in the process of weaning off NIV.

Parents or carers (adults with parental responsibility) of eligible children will be able to take part, unless they are members of the SPIRITUS study steering committee, took part in Phases I and/or II or were involved in the PPI activities around intervention development. Each parent-child dyad will be able to participate in hase III once.

In Phase III, we will aim to recruit 10–12 parent-child dyads. These sample sizes are in line with other similar feasibility/acceptability studies; they will provide an insight into how acceptable both the interventions in the toolkit and the data collection methods used in the study are to families.^28 29^ Unlike in Phases I and II, parent-child dyads will not be able to participate independently. Parents who wish to participate must also consent for their child’s participation and children cannot take part if their parent does not also consent to participate.

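### In Phase III families given a clinical change, the usage baseline normally precedes the change and the test follows it, so the comparison mixes the change with the toolkit

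*Protocol article*

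**What the plan says.** The Quantitative analysis section of the protocol article sets out the comparison. The test window is given as: "We will compare usage data (number of hours used per night and number of nights used) during the 2-week trial period". The comparator is "usage data from the 4 weeks prior to the most recent ventilator download (usually in the NIV clinic or at the most recent sleep study").

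The Phase III Data collection section sets the timing of the test: "Families who have a recommended clinical change will be asked to start testing the intervention 2 weeks after the introduced change", whereas "families with no clinical changes will be asked to start immediately". The changes it has in mind include a new interface, altered pressure settings or an added comfort measure. It also says who will tend to receive one: appointments with "families who have lower levels of adherence will be more likely to result in a recommended clinical change".

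On other baseline measures the same section says: "After the initial consultation, the researcher will collect baseline data related to the intervention and outcome from families". Of the ventilator and Actiwatch data collected at the end of the test it says: "These data will also be collected to assess whether the intervention has caused a decrease in adherence".

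On sample size: "In Phase III, we will aim to recruit 10–12 parent-child dyads". The Study outcomes section leaves efficacy to a later pilot study.

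**The concern.** The 2-week wait looks designed to let a clinical change take effect before the toolkit intervention is tested. It can separate the two only if the baseline is read during the wait. The stated baseline is instead tied to a download usually made at the clinic or sleep study, when the change has normally not yet taken effect. The nights that could separate the two effects are not used in the comparison.

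The usage log is the objective check in Phase III, and the protocol asks of it whether the intervention reduced adherence. In changed families a better mask could raise usage while a burdensome intervention lowers it, and the comparison would show the sum. Lower-adherence families are those the protocol expects to receive changes, so the check is weakest where it matters most.

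**Working it through.** **Plan's own figure.** There is none to reproduce: the article gives no expected change in usage, no standard deviation and no power calculation for Phase III.

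**Step 1: timeline.** Let day 0 be the appointment with the download, and let a change be introduced on day c, with c at or after 0.

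| | Baseline nights | Change | Test nights |
|---|---|---|---|
| Change recommended | day −28 to −1 | day c | from day c + 14, for 14 nights |
| No change | day −28 to −1 | none | from about day 0, for 14 nights |

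In the first row no baseline night follows the change and every test night does. In the second row the problem does not arise.

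**Step 2: does the word *usually* rescue it?** Take the most favourable case, a download on the day the test starts (day c + 14). The 28 nights before it run from day c − 14 to day c + 13: 14 before the change and 14 after. So a 4-week window ending no later than the test start has at most 14/28 = half of its nights after the change.

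**Step 3: size of the mixing.** Assume the toolkit has no effect and a clinical change adds e h/night. The documents give neither e nor the share of families with a change, so both are assumptions.

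- Shift in changed families = e.
- Shift in the pooled mean = (families with a change / all families) × e.

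| Families with a change | e = 0.5 h | e = 1.0 h |
|---|---|---|
| 3 of 12 | 3/12 × 0.5 = 0.125 h | 0.25 h |
| 6 of 12 | 6/12 × 0.5 = 0.25 h | 0.50 h |
| 9 of 12 | 9/12 × 0.5 = 0.375 h | 0.75 h |

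Five of 10 gives the same result as 6 of 12. In the favourable case of Step 2 these shifts are halved.

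**Step 4: masking.** Observed difference in changed families = toolkit effect + e. If the intervention lowers usage by 0.5 h/night and e = 0.5, the result is −0.5 + 0.5 = 0. With e = 1.0 it is −0.5 + 1.0 = +0.5 h. A real fall appears as no change or as a gain.

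**Step 5: regression to the mean, as a side check.** Assume window means are normal with mean 4.6 h (midpoint of the 4.0 to 5.2 h average quoted in the Introduction), SD 2.5 h, correlation ρ between windows of 0.7 to 0.9, and low adherence approximated as a baseline mean below 4 h. Then z = (4 − 4.6)/2.5 = −0.24, with normal density 0.388 and lower tail 0.405.

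- Low group: (1 − ρ) × 2.5 × 0.388/0.405 = +0.24 h (ρ = 0.9) to +0.72 h (ρ = 0.7).
- High group: −(1 − ρ) × 2.5 × 0.388/0.595 = −0.16 h to −0.49 h.
- Equal mix: (0.24 − 0.16)/2 = +0.04 h to (0.72 − 0.49)/2 = about +0.11 h.

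The two groups move in opposite directions and largely cancel.

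**The case against.** **Phase III is a feasibility and acceptability study.** Usage is reported descriptively, no test is planned and efficacy is deferred. The first stated use of the ventilator data is to see whether NIV was used in the 2 weeks and during sleep, as a check on parent reports. That needs no baseline. This stands, and a reader might wrongly infer that the protocol plans to credit the toolkit with a benefit: it plans no such conclusion. What remains is the one question that does need a baseline, whether the intervention caused a fall, and the comparison cannot answer it for changed families.

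**The sizes are assumed.** They are. On the Step 5 SD, and with correlations from 0.6 to 0.9, the standard error of the mean difference is 2.5 × √(2(1 − ρ))/√n. That runs from 2.5 × √0.2/√12 = 0.32 h to 2.5 × √0.8/√10 = 0.71 h, so the pooled shift is of the same order as the noise. But the shift has a systematic direction if changes help, and it sits undiluted in the changed families.

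**Splitting families by clinical change is analysis-plan detail.** On its own that would be fair, and extracting clinical information for analysis leaves room for it. The baseline window, however, is stated in the article, and a split alone still leaves changed families without a usable comparison.

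**Use may still be settling in the nights right after a change.** This is a fair limit on any baseline taken there, and a reason to show both baselines.

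**Conclusion.** The point holds for families who receive a recommended clinical change. Their stated usage baseline normally precedes the change, their test period follows it, and the difference cannot be assigned to the intervention in either direction. If a change is worth 0.5 to 1.0 h/night, changed families shift by that amount, and the pooled mean by 0.25 to 0.5 h/night if half of the 10–12 families have one. Both the effect and the share are assumptions. Families without a change are not affected.

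Two stronger readings are not supported:

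- A reader might infer that baseline outcome data are also taken before the change. The Data collection section places them after the initial consultation and does not say whether the change has been introduced by then. All that can be said is that their timing is not tied to the start of the test.
- A reader might infer a general upward bias from regression to the mean. That requires the same download to have set the child's adherence category, which is not stated. The sampling matrix also aims for equal numbers across adherence levels, so the effect largely cancels overall. It is a secondary caution when reading the high- and low-adherence subgroups.

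**What to change.** Leave the 2-week wait as it is and change only the measurement and reporting:

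1. **Primary usage baseline.** For families with a change, use the nights between the change and the first test night. For families without one, use the 14 nights immediately before the first test night. Read both from the download already planned after the test, as far back as the device log allows; the article states no log length, so this should be checked.
2. **Second baseline.** Keep the 4 weeks before the clinic or sleep-study download, labelled as pre-change where a change was made.
3. **Reporting.** Show families with and without a change separately, against both baselines.
4. **Baseline outcome questionnaire.** Tie it to the start of the test, by phone for delayed starters.
5. **Wording.** Replace the causal statement about a decrease with a descriptive one: whether usage in the test was lower than in the nights just before it.

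**Cost.** Protocol and analysis wording, plus one extra phone contact for delayed starters. No new families or equipment are needed.

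**Downsides.** A 14-night mean is noisier than a 28-night mean, by √(28/14) = 1.41 in standard error if nights were independent. Use may still be settling after a change, so a trend could remain in the primary comparison. For immediate starters whose download was made at the same appointment, the new window is roughly the later half of the existing one, so they lose some precision and gain little.
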